### Measures

#### Clinical assessment

Demographics, medical history, medication use, cardiovascular risk factors (eg, diabetes, hypercholesterolaemia, hypertension) and behavioural risk factors (eg, smoking, alcohol consumption) are recorded based on electronic medical records and by interviewing participants at baseline. Clinical details of the most recent stroke are assessed, where relevant. Blood pressure and heart rate are measured after the participant has been seated comfortably for at least 5 min. Three measurements are collected, and means are calculated as the average of the last two readings. Height and weight are recorded to determine body mass index. Global disability is assessed using the Modified Rankin Score (mRS).^26^ At long-term follow-up visits, we record incident clinical events and changes in medication use and cardiovascular risk factors.

#### Neuroimaging

All participants undergo brain MRI, acquired at both sites on identical 3T scanners (MAGNETOM PrismaFit, Siemens Healthineers, Erlangen, Germany) with a 32-channel head coil. The acquisition protocol consists of the following sequences: three-dimensional (3D) T_1_-weighted magnetisation prepared rapid gradient echo (MPRAGE), 3D T_2_-weighted fluid-attenuated inversion recovery (FLAIR), 3D T_2_*-weighted susceptibility weighted imaging (SWI, Cambridge) or quantitative susceptibility mapping (QSM, Nijmegen), intravoxel incoherent motion imaging (IVIM, Nijmegen only), multishell diffusion-weighted imaging (DWI)^27–29^ and dynamic contrast enhanced (DCE) imaging (online supplemental table 1). DWI is acquired twice with opposing phase-encoding directions to enable correction for magnetic field and eddy current-induced geometric distortions. A B_0_ field map and an additional b=0 s/mm^2^ image with opposed phase-encoding polarity are acquired to correct for geometric distortions in IVIM imaging.

10.1136/bmjopen-2024-084303.supp1Supplementary data

The study employs an optimised DCE-MRI protocol,^17^ which has been implemented in other studies conducted by the Cambridge research group.^9^ This uses a fast T_1_ mapping approach based on variable flip angle (VFA) spoiled gradient echo (SPGR) imaging, before and after the injection of a gadolinium-based contrast agent. Following one precontrast T_1_ mapping acquisition, a 0.025 mmol/kg dose of the gadolinium agent gadoterate meglumine (Dotarem, Guerbet, Villepinte, France) is administered by a medically qualified staff member. Postcontrast T_1_ mapping is started 1 min after administration and continued for approximately 20 min (seven time points) to map the signal changes that are used to calculate permeability.

T_1_-weighted MPRAGE images will be processed using standard imaging processing pipelines (eg, SIENAX) to obtain maps of grey matter, white matter and cerebrospinal fluid. Image output will be visually inspected for misclassifications, and then used in conjunction with WMH masks to estimate brain and tissue volumes. Diffusion imaging data are preprocessed using the FMRIB Software Library^30^ and MRtrix3 (mrtrix.org). Specifically, we will perform denoising, Gibbs artefact removal and correction for head motion, eddy current distortions and susceptibility-induced distortions. Diffusion data will be analysed using voxel-by-voxel maps of standard diffusion parameters (eg, MD, FA) to produce whole-tissue histograms. Additionally, peak width of skeletonised mean diffusivity (PSMD)^31^ will be derived from DTI. PSMD is calculated from tissue on a white matter skeleton and is a measure of the width of the MD histogram. For DCE analysis, T_1_ maps are first computed based on the VFA SPGR images using the scanner software (MAPIT package, Siemens Healthineers), correcting for B_1_ inhomogeneity using a separately acquired precontrast B_1_ map. The T_1_ maps are spatially coregistered for motion correction, and pharmacokinetic analysis is performed on a voxel-by-voxel basis using the Patlak model,^32^ yielding maps of K_trans_, the blood-to-tissue transfer constant. The T_1_ maps—and hence the K_trans_ maps—are also registered to the conventional images and used for analysis alongside manually delineated lesion masks. IVIM images will be processed and analysed as described previously.^33^

Participants will also be assessed on four SVD markers, namely WMH, lacunes, cerebral microbleeds (CMB) and perivascular spaces (PVS), according to the STRIVE-2 criteria.^23^ All scans will be visually assessed by trained raters, blinded to all demographic and clinical information. WMH maps will be obtained from FLAIR images using an automated tool. Lesion maps will be reviewed by a single trained rater blinded to all clinical information and manually corrected for misclassifications. Haemorrhages and isolated lacunes will be excluded from the WMH mask. WMH volumes will be extracted from the finalised lesion masks and normalised by total intracranial volume. WMH will also be assessed semiquantitatively through visual rating.^34^ Periventricular and deep WMH will be rated separately. Lacunes and PVS will be identified manually using T_1_-weighted and FLAIR images and delineated to produce lesion maps. PVS, CMB and lacunes will also be rated semiquantitatively using validated scales where available.^35^ PVS will be assessed separately in the basal ganglia and centrum semiovale to account for different underlying pathologies. CMB will be manually delineated using SWI (Cambridge) and QSM images (Nijmegen) to derive CMB lesion maps.

#### Blood samples

Non-fasting, venous blood samples are drawn at baseline and 2-year follow-up by qualified clinical personnel. Blood withdrawal is performed before MRI to ensure that the injected gadolinium-based MRI contrast agent does not interfere with laboratory tests.^36^ Blood samples are collected at approximately the same time of day for all participants to minimise circadian-related variation in inflammatory and coagulation markers.^37^ At baseline, blood is collected in EDTA tubes for plasma, serum tubes for serum and BD Vacutainer CPT tubes (BD Biosciences) for whole blood and PBMCs. Blood tubes are stored at room temperature and processed within 2 hours after collection for the following procedures:

PBMCs are isolated using sodium heparin CPT tubes following manufacturer recommendations and freshly stimulated for 24 hours with the TLR-4 agonist lipopolysaccharide (LPS), with the TLR-2 agonist Pam3Cys-Ser-(Lys)4, with LPS plus the inflammasome activator Nigericin, or with RPMI buffer as control. Supernatants are stored at −80°C for future analysis of cytokines and chemokines.Comprehensive immunophenotyping of fresh whole blood is performed by using Cytometry by Time-Of-Flight (CyTOF).Isolated PBMCs are viably frozen to allow future single-cell RNA sequencing (scRNA-seq), Assay of Transposase Accessible Chromatin with high-throughput sequencing (ATAC-seq) and regulatory T cell (Treg) suppression assays. ScRNA-seq, ATAC-seq and Treg suppression assays will be performed after completion of the study in subgroups of patients with the highest and lowest progression rates of SVD.A panel of circulating inflammatory markers is measured in serum using the Olink proteomics platform (Olink Proteomics AB, Uppsala, Sweden).

At 2-year follow-up, blood will be collected in EDTA tubes and processed according to manufacturer’s instructions. Plasma will be stored at −80°C for future analysis of circulating inflammatory and coagulation markers.

#### Neuropsychological assessment

At baseline and 2-year follow-up, participants undergo cognitive assessment using a test battery designed to capture characteristic cognitive impairment in SVD (online supplemental table 2). Tests have been selected that are validated and normed for use in both countries and languages (English, Dutch); for a more extensive description of each test see Lezak *et al*.^38^ Premorbid intelligence is assessed using the UK-developed National Adult Reading Test (NART-Revised) in Cambridge, and its Dutch equivalent (Dutch Adult Reading Test) in Nijmegen. Processing speed is measured using the Symbol Digit Modalities Test (Written) and the Trail Making Test A. Working memory is measured using the forward and backward conditions of the Digit Span subtest of the Wechsler Adult Intelligence Scale-Fourth Edition. Executive function is assessed using the Trail Making Test B and the Brixton Spatial Anticipation Test. Visuospatial ability is evaluated using the Rey-Osterrieth Complex Figure Test (RCFT)-Copy trial. Memory is measured using the RCFT-Recall trial and the Story Recall subtest from the Rivermead Behavioural Memory Test-3. The results of all tests will be converted to age-adjusted, education-adjusted and/or sex-adjusted standard scores using published country-specific normative data.

Self-administered questionnaires to assess psychological symptoms and social functioning are performed at the beginning of study visits to avoid responses being impacted by tiredness and affective changes from the clinical interview and cognitive tests. Depressive symptoms are assessed using the 30-item Geriatric Depression Scale.^39^ Apathy is evaluated using the Apathy Evaluation Scale.^40^ Fatigue is assessed using the Fatigue Severity Scale.^41^ Social cognition is assessed using the Social Norms Questionnaire.^42^

#### Gait assessment

Gait assessment is carried out at baseline and 2-year follow-up using the Timed Up and Go (TUG) test and the 6 m walk test. The TUG assesses gait performance and balance and is measured as the time (seconds) it takes a participant to rise from a chair, walk 3 m, turn around, walk back to the chair and sit back down. The 6 m walk test determines gait speed (metres/seconds). Participants have to walk a distance of 10 m, and gait speed is assessed over a 6 m distance by timing the participant from the 2 m point to the 8 m point. Participants are instructed to walk at a comfortable pace during both tests. The use of walking aids is recorded, if applicable. Both tests include a practice trial, followed by three timed trials which are averaged.

### Data analysis

Peak height of the MD histogram was selected as the primary endpoint, given our past demonstration that it is the most sensitive DTI marker for SVD progression.^43^ Based on longitudinal MRI data from the SCANS study, the yearly rate of change of MD peak height was −3.72×10^−4^ mm^2^/s (SD 3.12×10^−5^), which corresponds to an annual percentage change of −2.44%.^43^ This would equate to a change of −4.88% over the 2-year follow-up period of the INSVD study.

Our primary analysis will test whether baseline measures of inflammatory and immune markers predict SVD progression as measured by MD peak height. We assume a linear relationship between baseline levels of coagulation and inflammatory markers and the change in MD peak height. Therefore, we will run linear regression models and adjust for age, sex, education and other conventional MRI markers of SVD, where appropriate.

As our secondary objectives, we will assess (1) the relationship between inflammatory and immune markers and BBB permeability, both globally (cortical and subcortical volumes) and regionally (hotspot volumes) and (2) whether baseline levels of inflammatory and immune markers are associated with other imaging parameters, as well as cognitive and clinical outcomes. Similar to our primary analyses, we will conduct linear regression modelling to test these associations.

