## Methods and analysis

### Overview

The INSVD study is a prospective multicentre observational cohort study in patients with SVD. The research will be conducted at two sites—Cambridge (UK) and Nijmegen (The Netherlands)—each recruiting 100 participants (total n=200). At baseline and 2-year follow-up, participants undergo clinical and cognitive assessments, blood draw and brain MRI. Follow-up will be continued for the next 6 years to track incident clinical events, among others (figure 1). Study recruitment began in August 2022 and study visits (baseline and 2-year follow-up) are projected to be completed by August 2026.

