#### Exclusion criteria

Potential participants are excluded if they have any MRI contraindication, or an estimated glomerular filtration rate (eGFR) <60 mL/min/1.73 m^2^ (UK) or <30 mL/min/1.73 m^2^ (Netherlands) within the past 3 months (figure 2). If eGFR has not been assessed within the last 3 months, this is measured as part of the research procedure. Other exclusion criteria include strokes caused by factors other than SVD (eg, cardioembolic source, carotid or vertebral artery stenosis >50%), another diagnosed chronic neurological condition (eg, Alzheimer’s disease, Parkinson’s disease), myocardial infarction in the past year, vasculitis, autoimmune or autoinflammatory disease, treatment with immunomodulating drugs, known monogenic causes of SVD, or limited life expectancy due to another illness or chronic condition which would make the 2-year follow-up difficult (eg, widespread malignancy).

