#### Participant recruitment

At the Cambridge site, participants are screened and recruited from the clinical stroke service at Cambridge University Hospitals National Health Service Foundation Trust and patient registers of patients with SVD enrolled in previous research studies. Screening is conducted through electronic hospital records, discussions with the patient about relevant medical history, and through the local MRI safety questionnaire. ECG and carotid artery duplex scans have been performed as part of ischaemic stroke workup and are used to rule out stroke causes other than SVD.

At the Nijmegen site, participants are recruited from the Radboud University Nijmegen Diffusion tensor and Magnetic resonance imaging Cohort (RUN DMC) study,^24^ and the neurology outpatient clinic at Radboud University Medical Centre. Screening involves reviewing electronic hospital records and discussing medical history with the patient. ECG and carotid artery duplex scans are included as part of screening procedures, in case information on atrial fibrillation and large artery disease are not up to date or readily available from medical records.

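### The adjustment set for the pooled two-site regressions does not name site, although the sites differ in recruitment source and eGFR eligibility; a site term would cost almost nothing

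*Protocol article*

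**What the plan says.** The primary analysis regresses change in MD histogram peak height on baseline immune and inflammatory markers. For adjustment, the Data analysis section states "we will run linear regression models and adjust for age, sex, education and other conventional MRI markers of SVD, where appropriate". For the secondary objectives it adds "Similar to our primary analyses, we will conduct linear regression modelling to test these associations". The article nowhere names site, centre or country as a covariate, stratum or random effect.

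The same article describes how the two halves of the cohort differ:

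- **Size.** The Overview has two sites, "each recruiting 100 participants (total n=200").
- **Source.** Under Participant recruitment, in Cambridge "participants are screened and recruited from the clinical stroke service at Cambridge University Hospitals", and also from registers of earlier SVD studies. Nijmegen recruits from an existing imaging cohort and a neurology outpatient clinic.
- **Renal eligibility.** The Exclusion criteria set the eGFR exclusion at "<60 mL/min/1.73 m^2^ (UK) or <30 mL/min/1.73 m^2^ (Netherlands"), so only the Dutch half can include values from 30 up to 60.
- **Blood.** Under Blood samples, tubes are processed within 2 hours of collection, with fresh cell stimulation and fresh whole-blood cytometry.
- **Secondary measures.** Under Neuroimaging, "CMB will be manually delineated using SWI (Cambridge) and QSM images (Nijmegen) to derive CMB lesion maps". Under Neuropsychological assessment, test results become "standard scores using published country-specific normative data".

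**The concern.** Site is the basic design variable of a two-centre cohort, and the published adjustment set omits it. Two kinds of harm can follow.

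- **Confounding.** If one site has higher marker levels and also faster or slower MD change, the pooled regression shows an association even when none exists within either site. Shifts in opposing directions can also mask a true association.
- **Dilution.** If the sites differ only in the marker, for instance through laboratory handling, the between-site spread acts as noise in the exposure and weakens a true association.

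For the primary analysis the plausible routes are recruitment source, the renal range admitted and local handling of fresh blood. The last is an inference: the article does not say where each assay is run, but a 2-hour limit with sites in two countries makes local processing likely. The planned power is 80% with no reserve, so dilution matters as well as false positives.

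**Working it through.** **Inputs from the article.** r = 0.22, two-sided α = 0.05, power 80%, 160 evaluable, 20% loss, 200 recruited (Sample size calculation); 100 per site (Overview).

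**Assumptions.** Loss is equal by site, so 80 are evaluable at each. Site shifts are in within-site SD units. No other covariates are in the model.

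**1. The plan's own figure.** By the Fisher formula, n = ((1.960 + 0.842)/atanh(0.22))² + 3 = (2.802/0.2237)² + 3 = 159.9, so 160. Then 160/(1 − 0.20) = 200. Both stated figures reproduce.

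**2. Spurious correlation.** For two equal sites and a shift of d SD, the correlation between site and the variable is (d/2)/√(1 + d²/4). With no within-site association, the pooled marker–outcome correlation is the product of the two site correlations. For 0.5 SD in both: 0.25/√1.0625 = 0.2425, and 0.2425² = 0.059.

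**3. Type I error.** Simulated with 80 + 80 participants, 20,000 runs per row, nominal 5%. The Monte Carlo standard error at 5% is √(0.05 × 0.95/20,000) = 0.15 percentage points.

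| Marker shift (SD) | Outcome shift (SD) | Spurious r | Error without site | Error with site |
|---|---|---|---|---|
| 0 | 0.5 | 0.00 | 4.9% | 4.9% |
| 0.2 | 0.2 | 0.01 | 5.3% | 5.1% |
| 0.3 | 0.3 | 0.02 | 5.8% | 5.1% |
| 0.5 | 0.3 | 0.04 | 7.5% | 4.9% |
| 0.5 | 0.5 | 0.06 | 11.6% | 5.0% |
| 0.8 | 0.5 | 0.09 | 20.5% | 4.7% |
| 0.8 | 0.8 | 0.14 | 42% | 5.2% |
| 1.0 | 1.0 | 0.20 | 73% | 5.0% |

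At 0.5/0.5 the Fisher approximation gives about 11%, in line with the simulated 11.6%.

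**4. Dilution when only the marker shifts.** The pooled correlation is r/√(1 + d²/4). For d = 1: 0.22/√1.25 = 0.197. At n = 160, power = Φ(atanh(0.197) × √157 − 1.960) = Φ(0.54), about 70%.

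**5. Cost of a site term.** With k extra covariates the Fisher variance is 1/(n − 3 − k). For k = 1 and the same partial r = 0.22, the required n is 159.9 + 1 = 160.9, so 161. At n = 160, power = Φ(0.2237 × √156 − 1.960) = 79.8%, against 80.0% with k = 0.

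**The case against.** **A condensed article is not a closed list.** The Data analysis section covers all modelling in a few sentences and ends its covariate list with a qualifier on appropriateness. A centre term is often left to the analysis plan, which is not shown. A reader might infer that the sponsor has decided to exclude site. The article does not say so; it only fails to name it. What remains is that the article does commit to named covariates. The qualifier governs those and does not bring in site, so following the text as written leaves site out.

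**Most site differences do not reach the primary outcome.** A reader might infer that every listed difference biases the primary result. It does not. MD peak height comes from diffusion imaging listed for both sites on identical 3T scanners, and the outcome is a within-person change, which cancels constant scanner offsets. The SWI/QSM difference and the Nijmegen-only IVIM sequence do not produce MD. SWI versus QSM matters for microbleeds as a secondary outcome, or if they serve as a covariate. Country-specific norms bear on cognitive outcomes only and partly correct for country. This objection stands. It leaves recruitment source, eGFR range and local blood handling as the routes for the primary analysis.

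**The size is assumed.** No site-level figures are given. At shifts of 0.2 to 0.3 SD the inflation is trivial, and with a shift in the outcome alone there is none. Both sites share the same core inclusion criteria, and age, sex, education and MRI markers may absorb part of any case-mix difference, so the table overstates the error to that extent. This also stands. Those covariates cannot be relied on to absorb all of it, least of all a laboratory offset.

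**Conclusion.** The point holds as a recommended clarification. The published adjustment set does not name site in a pooled two-site analysis where the article itself documents differing recruitment sources and eGFR eligibility. Under the assumptions stated, type I error runs from about 5.3% (0.2 SD shifts in both variables) through 11–12% (0.5 SD) to 42% (0.8 SD). A 1 SD shift in the marker alone cuts power from 80% to about 70%. Where in this range the study would fall cannot be told from the article.

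A reader might go further and conclude that the pooled associations will be site artefacts. The article does not support that: it shows reasons why the sites could differ, but no measured difference in any marker or in MD change. The case for acting rests on the imbalance between a possible distortion and a negligible cost.

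**What to change.** Name site as a fixed covariate in every pooled primary and secondary model. Report the marker-by-site interaction, or site-specific estimates, as a consistency check. State both before the analysis, so that the choice between site-adjusted and unadjusted results is not made after seeing them. Include microbleed and normed cognitive outcomes in the same rule.

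The cost is one degree of freedom (evaluable n 160 to 161, or power at 160 from 80.0% to 79.8%) and a sentence or two in the analysis section. Site is known for every participant, so recruitment and measurement do not change.

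Adjustment for eGFR and standardisation of laboratory markers within site are optional sensitivity analyses. Renal function may lie on a shared vascular pathway, so adjusting for it is a debatable causal choice. The site term already removes mean shifts, so standardisation adds only a correction of scale. No view is taken on which eGFR cut-off is right.

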### Patient and public involvement

This research has been informed through consultation with external stakeholders, including patients and their families, both in the UK and Netherlands. In joint initiatives with the Stroke Association (UK), SVD and cognitive decline have been identified as major priorities for patients with stroke. In a joint funder working group attended by both patients and their families, funders and health professionals, research into the mechanisms underlying SVD was identified as a top priority. Study protocols were developed in partnership with local stroke support groups who advised on the study and logistics of implementation. To ensure that participants understand the study clearly before enrolment, the participant information sheet was reviewed by two patient volunteers, whose comments were incorporated into the final document.

### Ethics and dissemination

The study is conducted in accordance with the principles of the Declaration of Helsinki, the conditions and principles of Good Clinical Practice, and the applicable local regulatory requirements and laws. The project is funded by a joint grant from the British Heart Foundation and Dutch Heart Foundation (ref: SP/F/22/150028) and jointly sponsored by the Cambridge University Hospitals Foundation NHS Trust and the University of Cambridge in the UK, and the Radboud University Medical Centre in the Netherlands. Any participant-derived benefits resulting from this research, such as new insights into disease mechanisms or possible novel therapies, will be disseminated to study participants at patient groups and to members of the public through standardised communication platforms, including research journals and disease-specific national patient websites.

This study protocol has been registered on ClinicalTrials.gov (NCT05746221) and received ethical approval from the local ethics board (UK: East of England—Cambridge Central Research Ethics Committee (REC) ref: 22/EE/00141, Integrated Research Application System (IRAS) ID: 312 747. NL: Medical Research Ethics Committee (MREC) Oost-Nederland, file number: 2022-13623, NL-number: NL80258.091.22).
